### Plans to promote participant retention and complete follow-up {18b}

Head Start staff see/interacted with parent-child dyads on a daily basis, and so were able to promote retention and follow-up.

### Data management {19}

Head Start staff collected paper surveys and sleep logs. Researchers trained staff to enter data into site-specific REDCap secure databases. Paper surveys/logs were mailed back to the researchers who re-entered or corrected data as needed. Range checks were implemented. The original funding application identifies REDCap as the data storage system and double-entry.

## **Confidentiality {27}**

SPIRIT guidance: Data were collected from the parent participants- who completed surveys and logs themselves unless assistance was deemed of benefit- and entered by trained staff at the Head Start site. After data entry was complete, sites were no longer able to access the database.

## **Plans for collection, laboratory evaluation and storage of biological specimens for genetic or molecular analysis in this trial/future use {33}**

NA- there were no such specimens in the study.

## **Statistical methods**

### **Statistical methods for primary and secondary outcomes {20a}**

#### **STATISTICAL ANALYSIS PLAN**

Summary statistics of continuous variables were calculated as means and standard deviations; frequency distributions (n and %) are shown for discrete variables. To analyze treatment effect we fitted multi-level generalized linear models with the study outcome variables as dependent variables, an indicator for post-intervention status, indicators for the study phase (follow-ups 1 through 4, baseline as reference category), and covariates to adjust for age, child sex, Hispanic ethnicity, and race. Random intercepts at the agency and participant levels were included. For continuous outcomes (sleep duration, questionnaire scale scores) the identity link and gaussian error family were used. The coefficient of the post-intervention indicator is the estimate of the average treatment effect and is presented along with its 95% confidence interval (CI). For the dichotomous outcomes (positive Tayside questionnaire, parent-reported sleep problem), the log link and logistic error family were used. In this model the treatment is the odds ratio (exponentiated coefficient) of the post-intervention indicator, presented with its 95% CI.

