### Objectives {7}

This was a primary prevention trial of sleep health interventions in Head Start. This RCT of multi-level interventions grounded in the social-ecological model examined the following outcomes at ~9- and 12-month follow-up: a) child sleep duration, b) child sleep difficulties, and c) parent knowledge, attitudes, beliefs, and self-efficacy (KASB) regarding children's sleep.

-SLEEP DURATION (CHILD): Hypothesized differences in sleep duration for Intervention vs. Control periods were: a) longer duration for Intervention periods (Primary Outcome: difference at FU3 [app. 9 month follow-up]), b) >30-minute difference at FU3, and c) a 15-minute difference in duration at FU4 (app. 12 months). Sleep duration was measured via parent-reported sleep logs.

-SLEEP DIFFICULTIES (CHILD): Hypothesized differences between Intervention vs. Control periods were: a) lower mean total scores, b) lower odds of scores  $\geq 8/36$  and c) fewer parents reporting a sleep problem in the 10th Tayside item (Yes/No). Surveys with at least 7 of 9 items scored were included in analysis. The Tayside Children's Sleep Habits Questionnaire was used to assess this outcome. (Secondary outcome)

-KNOWLEDGE-ATTITUDES-SELF EFFICACY- BELIEFS (PARENT): Hypothesized differences in parents'

KASB for Intervention vs. Control periods were: a) higher KASB total scores and b) higher scores for each domain. KASB scales with at least 80% non-missing responses were included in analysis. The KASB survey was developed to align with the main educational intervention, the Early Childhood Sleep Education Program. (Secondary outcome)

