## **Trial design {8}**

Stepped Wedge Cluster Randomized Controlled Trial. The 7 agencies were randomized: 4 agencies (and 12 sites that operate under them) and 3 agencies (and 11 sites that operate under them) were randomized to Wedge 1 and Wedge 2, respectively.

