## Outcomes {12}

Outcomes were parent-reported school-night sleep duration per sleep logs (primary: at 9 months; secondary: at 12 months), mild/moderate sleep difficulties per validated questionnaire, and KASB total and domain scores at 9 and 12 months (secondary)

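### The single post-intervention coefficient cannot give or separate the FU3 (primary) and FU4 (secondary) effects, and it equals an average over treated periods only under an unstated assumption such as a constant effect

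*Combined protocol and SAP*

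**What the plan says.** Objectives {7} makes FU3 primary for sleep duration ("Primary Outcome: difference at FU3 [app. 9 month follow-up") and then hypothesises a ">30-minute difference at FU3, and c) a 15-minute difference in duration at FU4 (app. 12 months"). Outcomes {12} repeats the two time points ("primary: at 9 months; secondary: at 12 months").

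The model in Statistical methods {20a} contains "an indicator for post-intervention status, indicators for the study phase (follow-ups 1 through 4, baseline as reference category"), plus age, sex, ethnicity and race. It adds that "Random intercepts at the agency and participant levels were included". The reported result is then defined: "The coefficient of the post-intervention indicator is the estimate of the average treatment effect". The same indicator serves the Tayside and KASB outcomes. The section specifies no interaction with phase, no time-since-intervention term and no comparison with 30 or 15 minutes. Methods for additional analyses {20b} supplies none either.

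Trial design {8} has two sequences: "4 agencies (and 12 sites that operate under them) and 3 agencies (and 11 sites that operate under them"). Participant timeline {13} and section {18a} place FU3 one week after the Wedge 2 intervention and FU4 a year after baseline.

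**The concern.** The objectives name effects at two follow-ups and expect different sizes. The model returns one number, and nothing says which follow-up it describes. The design makes this worse than a labelling gap: from FU3 on, every agency has had the intervention, so no untreated group exists at either named time point. If the coefficient is reported as the answer to the primary question, readers will take it as the FU3 effect, when it mostly reflects November 2018 and January 2019. It could also conceal an effect that fades, or understate one that builds.

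**Working it through.** **1. The plan's own figure.** Sample size {14} gives 90% power for 15 minutes with n=173 at two-sided 0.05. No SD, ICC or within-child correlation is stated, so this cannot be reproduced. Back-solving: SE = 15/(1.960+1.282) = 4.63. The implied SD is 4.63×√173 = 60.9 minutes for a paired difference, or 60.9/√2 = 43.0 with 173 unpaired per phase. Either way it describes one intervention-versus-control contrast, not an FU3 contrast.

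**2. Who is treated when** (Participant timeline {13}; in brackets, months since that wedge's first post-intervention log).

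| | Baseline | FU1 Nov 2018 | FU2 Jan 2019 | FU3 Mar 2019 | FU4 Sept 2019 |
|---|---|---|---|---|---|
| Wedge 1 (4 agencies) | control | treated (0) | treated (2) | treated (4) | treated (10) |
| Wedge 2 (3 agencies) | control | control | control | treated (0) | treated (6) |

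**3. What the coefficient weighs.** Let D0 to D4 be the Wedge 1 minus Wedge 2 difference in means at baseline to FU4. Phase indicators remove anything common to both wedges. For an agency mean, let b = agency variance + child variance/m (shared across periods) and e = residual variance/m. Generalised least squares with random intercepts then gives

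coefficient = ½(D1+D2) − λ(D0+D3+D4), with λ = b/(e+3b).

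Assumed ranges, not in the documents: m 25 to 77 (77 ≈ 540/7), agency SD 0 to 20, child SD 20 to 40, residual SD 40 to 55 minutes. Covariates and missing data are ignored and agencies taken as equal in size.
- Weakest correlation (m=25, SDs 0, 20, 55): b=16, e=121, λ = 16/169 = 0.095.
- Strongest (m=77, SDs 20, 40, 40): b=420.8, e=20.8, λ = 420.8/1283.1 = 0.328.

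An effect equal in both wedges at FU3 makes D3 = 0 and so contributes nothing; the same holds at FU4.

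**4. Expected coefficient against the truth.** The treated-period mean is (4×sum of Wedge 1 effects + 3×sum of Wedge 2 effects)/22, since 4×4+3×2 = 22 agency-periods are treated. FU3 and FU4 truths are weighted 4:3. Minutes throughout; 30 stands in for more than 30.

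| True effects (Wedge 1 FU1-FU4; Wedge 2 FU3-FU4) | Coefficient | Treated-period mean | FU3 truth | FU4 truth |
|---|---|---|---|---|
| Constant 30 | 30.0 | 30.0 | 30 | 30 |
| By follow-up: 30, 30, 30, 15; 30, 15 | 30.0 | 555/22 = 25.2 | 30 | 15 |
| Linear decay: 30, 27, 24, 15; 30, 21 | 28.5+12λ = 29.6 to 32.4 | 537/22 = 24.4 | 26.6 | 17.6 |
| Growing by step: 15, 20, 25, 30; 15, 20 | 17.5−20λ = 10.9 to 15.6 | 465/22 = 21.1 | 20.7 | 25.7 |
| None until FU3: 0, 0, 30, 15; 30, 15 | 0.0 | 315/22 = 14.3 | 30 | 15 |

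Linear decay loses 1.5 minutes a month (15 minutes over 10 months).

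**5. Can time-specific terms be added?** Post×FU3 and post×FU4 equal the FU3 and FU4 phase indicators, because everyone is treated then: the design matrix has rank 6 for 8 columns. Terms by number of measurements since intervention are estimable (rank 9 of 9), but they treat Wedge 1 at 2 months and Wedge 2 at 6 months as the same exposure. Terms by elapsed months are not all estimable (rank 9 of 10). D3 gives the 4-month effect if both wedges share the 1-week effect, but D4 gives only the 10-month minus the 6-month effect.

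**6. Precision, relative to the all-period single-indicator SE.**
- Pooled FU1-FU2 effect from baseline to FU2: (e+3b)/√((e+b)(e+5b)).
- Separate FU1 and FU2 effects: √[2(e+2b)(e+3b)/((e+b)(e+5b))].

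For b/e from 0.9 to 11.6 (the upper value is SD 45, ICC 0.05, within-child correlation 0.6, 77 per agency), these are 1.14 to 1.31 and 1.41 to 1.53. At the corners in step 3 (b/e = 0.13 and 20.3) they are 1.02 and 1.32, and 1.37 and 1.54. A numerical fit puts the third and fourth exposure terms at about 2.3 to 2.6 times (2.0 at the weakest corner).

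**The case against.** One treatment indicator with period effects is a standard stepped-wedge analysis, the plan openly calls its output an average, and with a constant effect it is unbiased and the most precise choice. Objectives {7} speaks of intervention versus control periods, so the FU3 label could be read loosely. It gives no target at FU1 or FU2 and no decline by time since intervention. The 15 minutes at FU4 could be a detection target, since the same figure is the detectable difference in Sample size {14}.

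Much of this stands, and it limits the point. A reader might infer that the reported effect is simply biased, or that it will exceed any effect ever present. The documents support neither. Bias depends on how the effect changes. Read by follow-up, the hypotheses give a coefficient of exactly 30, the true FU1-FU2 effect. Exceeding 30 needs an added decay by time since intervention, and even then the range starts at 29.6.

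The objection does not rescue the FU3 and FU4 objectives. The plan does not state the constant-effect assumption, its own hypotheses differ between the two follow-ups, and the coefficient contains no separate information about either.

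**Conclusion.** The mismatch holds without any numerical assumption: the model cannot give or separate the primary FU3 and secondary FU4 effects, and its interval does not test the hypothesis above 30 minutes or the 15-minute hypothesis. The cause is the lack of a concurrent control from FU3 onward, so interaction terms cannot cure it.

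Bias as an average is conditional. There is none with a constant effect. If the effect changes with time since intervention, the coefficient is not the treated-period average: under the assumed linear decay it is about 5 to 8 minutes too high (29.6 to 32.4 against 24.4), and under the assumed growth about 5 to 10 too low (10.9 to 15.6 against 21.1). If effects vary only by follow-up, the coefficient equals the FU1-FU2 mean effect and may differ from the overall average in either direction. The documents do not fix the direction or the size; these figures are illustrations.

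**What to change.** 1. State that the randomised concurrent comparison is FU1-FU2, and report the pooled effect from baseline to FU2. Its SE is about 14 to 31% larger than the all-period model's (extremes 2 and 32%). Separate FU1 and FU2 effects cost about 41 to 53% each (extremes 37 and 54%). This estimate does not test the FU3 hypothesis and should not be presented as doing so.
2. Replace or supplement the single indicator with time-since-intervention terms. State whether exposure is counted in measurements or months, and that the terms assume both wedges share the same effect at the same exposure time. Warn that later terms are imprecise (SE roughly 2.3 to 2.6 times).
3. State that the FU3 and FU4 effects, including the hypotheses of more than 30 and of 15 minutes, rest on that model and are not directly identified, and that the single coefficient and its interval do not test them.
4. If the single coefficient is kept, label it as assuming a constant effect, for the Tayside and KASB outcomes too.

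The trial is complete, so the added models are post hoc and should be reported as such. No new data are needed: the cost is revised wording, reanalysis and wider intervals. The absence of a concurrent control at FU3 and FU4 remains a design limit that wording cannot remove.

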## Introduction

### Background and rationale {6a}

Young children need sufficient, healthy sleep for optimal cognitive, social-emotional, and physical development, and to reduce obesity risk. At preschool-age (3-5 years), 10-13 hours of sleep per day inclusive of naps, is recommended. Yet, prior to school-entry up to one-third of US children don't sleep this much. Additionally, 25-30% of preschoolers experience difficulties falling and staying asleep, i.e., behavioral sleep problems (BSPs). Yet, optimal sleep hygiene practices at this age— a consistent bedtime and bedtime routine, falling asleep on one's own, limiting screen time before bed, etc.— are associated with fewer BSPs and longer sleep duration. Parent knowledge and attitudes about child sleep are significantly associated with the quality and quantity of young children's sleep. Generally, improved sleep hygiene and parent education are associated with positive effects on children's sleep and household routine, and no risks.

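### The link and error family named for the two binary sleep-difficulty measures do not fit the odds-ratio label; the model fitted needs to be stated correctly

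*Combined protocol and SAP*

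**What the plan says.** The model is described once, in the STATISTICAL ANALYSIS PLAN under Statistical methods for primary and secondary outcomes {20a}. Multi-level generalized linear models are fitted with a post-intervention indicator, study-phase indicators, covariates, and random intercepts for agency and participant.

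- Continuous outcomes: "the identity link and gaussian error family were used".
- Binary outcomes: the sentence opens "For the dichotomous outcomes (positive Tayside questionnaire, parent-reported sleep problem" and goes on to say that "the log link and logistic error family were used".
- Effect measure for the binary outcomes: "In this model the treatment is the odds ratio (exponentiated coefficient) of the post-intervention indicator", given with a 95% confidence interval.

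Objectives {7} states the hypothesis for the Tayside cut-off as "b) lower odds of scores" at or above 8 out of 36. For the tenth Tayside item it predicts only that fewer parents will report a problem, with no effect measure named. Sleep difficulties are a secondary outcome there.

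**The concern.** The specification and its interpretation contradict each other. With a log link, the exponentiated coefficient is a ratio of probabilities. With a logit link, it is a ratio of odds. The family name is also wrong: logistic is not an error family for a 0/1 outcome in a generalized linear model. The sentence on continuous outcomes names its link and family correctly, so a reader may take the binary sentence just as literally.

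Two things are at stake. An analyst who follows the text literally would fit a model that does not estimate the effect measure named for it, nor the odds hypothesis for the Tayside cut-off. And a reader of the results could not tell from the plan whether a reported ratio is a risk ratio or an odds ratio. For a common outcome these differ noticeably.

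**Working it through.** The plan gives no rate, effect or power figure for the binary measures, so there is no stated number to reproduce. The check is algebraic, followed by an illustration.

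**What each link estimates.** Let p0 and p1 be the probabilities in the control and intervention periods.

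- Log link: log(p) = a + b·x, so exp(b) = p1/p0, the risk ratio (RR).
- Logit link: log[p/(1−p)] = a + b·x, so exp(b) = [p1/(1−p1)] / [p0/(1−p0)], the odds ratio (OR).

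Binomial models with each link were fitted to the same two-group data, with fixed effects only. The log link returned the RR and the logit link the OR in every scenario tried.

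**Inputs for the illustration.**

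- Control prevalence of 25% and 30%: Background and rationale {6a} says "25-30% of preschoolers experience difficulties falling and staying asleep". This is a general background frequency, not the expected proportion at or above the Tayside cut-off.
- Control prevalence of 5% and 50%: assumed, to show the range.
- RR of 0.80: assumed.

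**Size of the gap.** With p1 = 0.80 × p0:

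- p0 = 0.05: p1 = 0.04, OR = (0.04/0.96)/(0.05/0.95) = 0.792
- p0 = 0.25: p1 = 0.20, OR = (0.20/0.80)/(0.25/0.75) = 0.750
- p0 = 0.30: p1 = 0.24, OR = (0.24/0.76)/(0.30/0.70) = 0.737
- p0 = 0.50: p1 = 0.40, OR = (0.40/0.60)/(0.50/0.50) = 0.667

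**Effect of misreading.** Suppose a log-link estimate of 0.80 is read as an odds ratio. The implied p1 is o/(1+o), with o = 0.80 × p0/(1−p0).

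- p0 = 0.30: o = 0.343, p1 = 0.255. The implied drop is 4.5 percentage points, against 6.0 for an RR of 0.80.
- p0 = 0.50: o = 0.800, p1 = 0.444. The implied drop is 5.6 points, against 10.0.

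This is algebra for two simple proportions. The planned model has agency and participant random intercepts, so its odds ratio is conditional on them and does not convert to percentage points in this way. The figures show that the label matters for a common outcome; they do not measure an error in this trial.

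**The case against.** The strongest reply is that log is a slip for logit. Three cues support it: the word logistic, the odds-ratio label in the next sentence, and the odds hypothesis for the cut-off in Objectives {7}. Only the word log points the other way. On that reading an ordinary mixed logistic regression was fitted, the odds-ratio label is right, and no reported effect changes. Moreover, the stated pair is not a standard specification, so an analyst would have had to interpret it before coding anything. This is the more likely reading.

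It is also fair to say that even the worse case has limited reach. The RR and OR lie on the same side of 1, and an interval that excludes 1 does so for whichever measure was fitted. In the illustration, reading the RR as an OR understates the benefit; it does not create one.

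What stands is that the only statement of this model is wrong as written on either reading. No other section names a logit link or a binomial family. The section on data access {31c} offers datasets on request but does not mention code, so an outside reader cannot resolve the question.

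A reader might infer that the published binary effects are mislabelled. The documents do not support that: it follows only if a log link was really fitted. A reader might also infer that the model would have failed to converge or given probabilities above 1. Those are general risks of log-link models and apply only in that same case. Nor are both binary hypotheses stated in odds; only the cut-off is.

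**Conclusion.** The text is internally inconsistent and needs correcting; confidence in that is high. Whether any reported effect carries the wrong label cannot be decided from the documents, and the wording makes it less likely than not. If a logit link was fitted, the error is confined to the names of the link and family. If a log link was fitted, two secondary results are risk ratios presented as odds ratios.

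The primary outcome, school-night sleep duration, is unaffected, as are the KASB scores and the Tayside mean score, because all of these use the identity link. Severity is minor to moderate. The RR-to-OR figures rest on an assumed effect and assumed prevalences, and leave out the random intercepts.

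**What to change.** Replace the specification for the binary outcomes with: *logit link and binomial (Bernoulli) family; the exponentiated coefficient of the post-intervention indicator is the odds ratio, conditional on the agency and participant random intercepts*. Then check this sentence against the model code.

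If the code used a log link, there are two acceptable routes. One is to refit with the logit link, which matches the odds hypothesis for the Tayside cut-off. The other is to disclose the log link and call the estimate a risk ratio throughout. The choice must not depend on which result looks better. The plan is written in the past tense and describes a completed trial, so the reason for the choice should be recorded.

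The cost is one sentence and one code check. Only if a log link turns out to have been run is there also a refit or relabelling of two secondary results.

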### **Interim analyses {21b}**

NA- there were no analyses planned until after the 12-month follow-up.

### **Methods for additional analyses (e.g. subgroup analyses) {20b}**

NA- there were no pre-planned subgroup analyses.

### **Methods in analysis to handle protocol non-adherence and any statistical methods to handle missing data {20c}**

NA- there was no such protocol

## **Plans to give access to the full protocol, participant level-data and statistical code {31c}**

The datasets generated during and/or analysed during the current study are available from the corresponding author on reasonable request

## **Oversight and monitoring**

### **Composition of the coordinating centre and trial steering committee {5d}**

NA- there was no coordinating centre or trial steering committee.

### **Composition of the data monitoring committee, its role and reporting structure {21a}**

No data monitoring committee proposal was submitted to the NIH or required by the IRB given that this was a low-risk health education (behavioral) intervention

### **Adverse event reporting and harms {22}**

NA- There were no plans to report adverse events as this was a low-risk behavioral intervention.

### **Frequency and plans for auditing trial conduct {23}**

NA- Trial is completed

### **Plans for communicating important protocol amendments to relevant parties (e.g. trial participants, ethical committees) {25}**

NA- there were no changes planned or made.

## **Dissemination plans {31a}**

Each agency's results were transmitted to the agency's executive directors. Findings will, we anticipate, be published in JAMA Network Open, and disseminated (upon publication) through Einstein College of Medicine/Montefiore Medical Center social media.

## **Discussion**

NA

